## Abstract

**Introduction:**

Cervical hybrid surgery (HS) combines anterior cervical discectomy and fusion (ACDF) and cervical disc arthroplasty (CDA) to establish an individualized surgical plan for patients with multiple cervical disc degenerative diseases. In order to maintain the stability of the spine after HS, an external cervical collar is often used. However, there is still controversy regarding the importance of a cervical collar following surgery. This study aims to determine whether the cervical collar is effective and how long it should be worn after surgery.

**Methods:**

This is a randomized, single-center, prospective, parallel-controlled trial. Eligible participants will be selected according to the inclusion and exclusion criteria. The primary outcome is the neck disability index, which will be evaluated before surgery and at one week, 3 weeks, 6 weeks, 3 months, 6 months, and 12 months following surgery. The secondary outcomes consist of the Japanese Orthopedic Association Scores, MOS 36-item short-form health survey (SF-36), visual analog scale, Pittsburgh Sleep Quality Index (PSQI), Bazaz dysphagia scoring system, Falls Efficacy Scale, cervical collar satisfaction score, neck soft tissue assessment, and Braden Scale, as well as radiologic assessments for cervical lordosis, disc height of the operative levels, fusion rate, range of motion (ROM), and complications including anterior bone loss, prosthesis migration, and heterotopic ossification. The clinical and radiologic examinations were performed by investigators with no therapeutic relationship with the individual patient. All radiographs were examined by one independent radiologist.

**Ethics and dissemination:**

The results of this study will be published in peer-reviewed journals and presented at conferences. Upon completion of this trial, our findings could provide an appropriate cervical collar-wearing guideline for patients receiving HS.

**Trial registration:**

ChiCTR.org.cn ChiCTR2000033002. Registered on 2020–05-17.

## Introduction

Cervical disc degeneration disease (CDDD), including cervical radiculopathy and myelopathy, is a common diagnosis among adult patients and causes significant disability and loss of productivity [1]. Anterior cervical discectomy and fusion (ACDF) was first introduced by Smith, Robinson [2] and Cloward in the 1950s [3] and has been considered the standard treatment for CDDD. ACDF can be utilized to decompress the anterior spinal cord and preserve the stability of the spinal column; however, multilevel ACDF may have a high risk of adjacent segment degeneration (ASD) [4–7]. Cervical disc arthroplasty (CDA) has been shown to be a safe and effective alternative to ACDF. In addition to maintaining physiologic motion, CDA can also restore disc height and some viscoelastic properties, ensure cervical segment mobility, as well as allow earlier return to normal activity [8]. Moreover, the incidence of ASD is significantly lower in patients that underwent ACDF. Nevertheless, the CDA approach is more expensive, and surgical indications are more restrictive [9]. Therefore, cervical hybrid surgery (HS) was proposed by combining ACDF and CDA in treating different levels to provide a better chance for cervical range of motion (ROM) protection and spinal reconstruction [10, 11].

Postoperative collar use provides several advantages, including the restriction of neck flexion, extension, lateral tilt, and rotation [12], and immobilization also reduces pain and provides spinal stability [13, 14], which makes it possible to reduce the risk of complications such as graft subsidence, displacement, and resorption [15–17]. Patients who undergo ACDF are always recommended to wear cervical collars to achieve the results mentioned above, while patients who undergo CDA are theoretically not required to wear collars since the implant prosthesis needs to maintain a physiological range of motion [18]. Collar usage after ACDF has been the subject of various studies in the literature, but there is no consensus on whether collars should be used. Some studies have suggested that collars restrict excess motion and are associated with improved postoperative outcomes [19–21]. In a prospective randomized controlled trial with patients receiving ACDF, the postoperative use of a cervical collar for the first six weeks was associated with a significantly lower neck disability index (NDI) [19]. However, several studies have reported different findings [22–26]. A Randomized clinical trial showed no statistically significant differences between braced and non-braced groups in NDI after 6 weeks post-operation [22, 25]. There was no statistically significant difference in 1-year postoperative Neck Disability Index scores between the brace and no-brace groups according to a prospective randomized control trial for patients who underwent ACDF [23]. Indeed, collar usage was correlated with a higher risk of pressure ulcers [12, 14], swallowing difficulty [27], coughing [28], and even marginal mandibular nerve palsy with long-term sensory degradation [29]. According to the questionnaires assessing the collar patterns of spine surgeons from 2009 to 2021 [30–32], surgeons may continue to use rigid collars primarily due to a lack of quality evidence directly comparing outcomes with or without bracing.

As a result, postoperative cervical collar use remains controversial, demonstrating the necessity of further research into the effects of collar use on clinical and radiographic outcomes after HS. The aim of this prospective, randomized control study was to investigate prospective physical, functional, and quality of life-related outcomes of patients undergoing HS, accompanied by the use of cervical collars for different periods of time.

## Methods

### Study design

This single-center, exploratory, prospective randomized controlled trial will be carried out at the West China Hospital of Sichuan University. Patients who fulfill study entry criteria will be randomly assigned to wear no collar, wear it for 3 weeks, wear it for 6 weeks, and wear it for 12 weeks at a ratio of 1:1:1:1. The study design and protocol were approved by the Ethics Committee on Biomedical Research, West China Hospital of Sichuan University. SPIRIT reporting guidelines were adhered to in this protocol [33].

**Fig. 1 Fig1:**
[figure not shown]
Flow diagram

### Sample size calculation

The sample size was calculated based on the data results of previous research. The target sample size was 80 (20 in each group). The sample size was calculated assuming NDI means of 10.0 for patients with collars and 5.00 for patients without collars after HS and a standard deviation of 5.00 [23–25], with 5% significance (a = 0. 005) and 90% power (b = 0.90) and considering a dropout rate of 20%. The sample size was calculated using PASS 15 software.

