## Discussion

External cervical brace fixation is often performed after anterior cervical surgery to provide biomechanical support to maintain spinal physiological curvature and stability, avoiding complications such as laryngeal edema and hematoma [47, 48]. There is still some debate regarding whether cervical collars should be used following surgery [24]. Previous studies have shown that the use of a cervical collar can reduce the risk of graft nonunion, graft displacement and sinking. At the same time, it can also restrict neck movement, providing spinal stability, reducing pain, and even increasing the sense of security in patients [20, 49]. Despite these benefits, some researchers have contested their validity. In their study, they found that patients with cervical pain that did not wear a cervical collar did not have a lower VAS score than those who wore a collar for 2 weeks. Moreover, the JOA score, SF-36, ROM, anterior convex angle, and complications were comparable between these two groups [50, 51]. In addition, wearing cervical collars can also bring many complications to patients, such as skin injuries skin ulcers, impaired daily activities and sleep, and decreased lung capacity and function [52–54].

Because there are no scientific clinical trials verifying the efficacy of cervical collars after hybrid surgery [20, 24, 26, 55–57], to explore the effect of wearing neck braces after undergoing hybrid surgery and discuss the best wearing time for recovery, we designed this randomized controlled trial, hoping to gain scientific and accurate results about the physical, functional, and quality of life-related outcomes of patients.

The process of osseointegration involves the direct structural and functional connection between living bone and the implant. This is normally initiated 6 weeks postoperatively, while the bone-graft bone bridge forms in around 3-month time. Therefore, most complications, including graft subsidence and loss of cervical lordosis appear during the first 6 weeks following surgery [58–60]. Thus, 3 months post-surgery is a critical time for recovery. In that case, the collar immobilization times were all set within 3 months post-surgery. Then, we adjusted the wearing time of the cervical collar to 3 weeks, 6 weeks, and 12 weeks.

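### The 5-point NDI gap behind the sample size is not shown to apply to hybrid surgery, and the planned four-arm analysis does not deliver the stated 90% power after dropout or cover the duration question

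*Protocol article*

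**What the plan says.** The Protocol article, Sample size calculation, opens with "The sample size was calculated based on the data results of previous research". It then gives the inputs: "assuming NDI means of 10.0 for patients with collars and 5.00 for patients without collars after HS and a standard deviation of 5.00 [23–25"]. Power is 90%, dropout is 20%, and the total is 80 patients, 20 in each of four arms (no collar, 3, 6 and 12 weeks). One mean serves all three collar arms, and no time point is named.

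Three other sections bear on these inputs.

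- **Introduction.** Reference 23 is a randomised trial in ACDF patients: "There was no statistically significant difference in 1-year postoperative Neck Disability Index scores between the brace and no-brace groups". Of reference 25, cited with 22, it says: "A Randomized clinical trial showed no statistically significant differences between braced and non-braced groups in NDI after 6 weeks post-operation [22, 25"]. Reference 24 appears only within the group 22–26, said to have findings different from the favourable ones, and its NDI result is not given separately. The one significant NDI result described (reference 19) is a lower score with a collar.
- **Discussion.** "Because there are no scientific clinical trials verifying the efficacy of cervical collars after hybrid surgery [20, 24, 26, 55–57"], which is given as the reason for doing the trial.
- **Statistical analysis.** Quantitative outcomes are compared by one-way ANOVA, followed by LSD or Dunnett's test. P values are two-sided and significance is set at 0.05.

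The Abstract gives two aims: whether the collar is effective, and how long it should be worn.

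**The concern.** The planning gap is a full standard deviation in favour of no collar. It is presented as coming from earlier research and labelled as a hybrid-surgery value. On the article's own account, at least one of the three cited sources studied a different operation, two found no significant NDI difference, and no trial in the target operation exists. No reason is given for carrying the figures over.

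Two further problems affect the 90% figure. It has to hold for the four-group analysis that will be run, on the patients left after the stated dropout. It also cannot speak to the duration aim, because the planning means for 3, 6 and 12 weeks are identical.

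At stake is how a null result is read. The Abstract says the findings could provide a collar-wearing guideline. If a non-significant result carries a 90% power label, readers may conclude that a collar is unnecessary or that the durations are interchangeable.

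**Working it through.** **Inputs.** Means 10 (each collar arm) and 5 (no collar), SD 5, 20 per arm and 20% dropout come from Sample size calculation. ANOVA and two-sided testing come from Statistical analysis. Completers per arm: 20 × (1 − 0.20) = 16. The significance level is printed both ways: "with 5% significance (a = 0. 005"). I use 0.05, which agrees with the words and with the Statistical analysis section.

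**1. Can the stated 80 be reproduced?**

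For the ANOVA with n per arm and one arm differing from the other three by d, the noncentrality is λ = n × Σ(mean − grand mean)² / SD². With means 5, 10, 10, 10 the grand mean is 8.75. The sum of squares is 3.75² + 3 × 1.25² = 18.75, so λ = n × 18.75 / 25 = 0.75n.

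- n = 20: λ = 15, power 90.2%. So 20 per arm gives 90% only if nobody drops out.
- Allowing for dropout: 20 / 0.8 = 25 per arm, total 100.

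Other readings at two-sided 5%:

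- One collar arm against no collar: 22 per arm by the normal approximation (23 by t-test). After dropout this is 28 (29) per arm, total 112 (116).
- No collar against all collar arms pooled, 1:3: 15 per arm, 15 / 0.8 = 18.75, so 19 per arm, total 76.
- ANOVA with two arms at 5 and two at 10: 16 per arm, 20 after dropout, total 80. This matches the total, but it is not the stated pattern, in which only one arm has no collar.

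Under the stated means, 80 including 20% dropout is not reproduced for the planned ANOVA or for a pairwise comparison.

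**2. Power with 16 completers per arm, at the assumed 5 points**

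- ANOVA: λ = 0.75 × 16 = 12 on 3 and 60 degrees of freedom; power 81%.
- One collar arm against no collar, t-test: noncentrality 5 / (5 × √(2/16)) = 2.83 on 30 degrees of freedom; power 78%.
- Collar arms pooled (16 v 48), not planned: noncentrality 5 / (5 × √(1/16 + 1/48)) = 3.46 on 62 degrees of freedom; power 93%.

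At alpha 0.005, if that were meant, the ANOVA power with 16 per arm would be 50%.

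**3. Sensitivity to the gap**

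The article gives no observed means or SDs from references 23–25. The smaller gaps below are therefore an assumed range, with SD kept at 5, and not estimates of what those trials found.

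| Gap (NDI points) | Four-group ANOVA | One collar arm v none | Pooled collars v none (unplanned) |
|---|---|---|---|
| 5 | 81% | 78% | 93% |
| 4 | 60% | 59% | 78% |
| 3 | 36% | 38% | 53% |
| 2 | 18% | 20% | 28% |

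**4. Duration**

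The planned differences between 3, 6 and 12 weeks are 10 − 10 = 0, so no power is defined for them. With 16 completers per arm, the gap between two durations detectable with 90% power (t-test, two-sided 5%) is 5.9 points. With all 20 per arm it is 5.3. Both exceed the whole 5-point effect assumed for collar against no collar.

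**The case against.** - **The hybrid-surgery label may describe the target population.** The sentence is framed as an assumption, and the citation follows the SD, so references 23–25 may be offered only for the SD. That is possible, but the section's opening sentence attributes the calculation to earlier results, and nothing calls 5 points a target or minimal important difference. The ambiguity needs resolving either way.
- **Non-significant does not mean no difference.** This stands. A reader might infer that the cited trials found no NDI gap, or one nearer 2 or 3 points. The documents report only the absence of statistical significance and give no means or intervals. Reference 24's NDI result is not described, so it could be the source of the figures.
- **The gap may still be true after hybrid surgery.** This stands. A reader might infer that the 5-point gap is wrong for these patients. The true gap is unknown, and ACDF is one component of hybrid surgery. The supportable statement is that the gap is not shown to apply.
- **Direction does not matter for power.** Correct: with two-sided tests, a 5-point gap has the same power either way. Reference 19 bears on the plausibility of the assumption and not on the 90%.
- **The pooled contrast exceeds 90%.** Also correct, and it is the contrast closest to the wording of the planning assumption. But the Statistical analysis section names ANOVA with LSD or Dunnett, not a pooled comparison.
- **The trial calls itself exploratory, and the sample size section claims no power for durations.** This limits the severity. It does not remove the need to say what the 90% covers, since duration is a stated aim. No section says that a null result will be read as equivalence; that risk is an inference.

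**Conclusion.** The point holds in three parts.

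1. The assumed gap is attributed to sources that, as the article describes them, do not establish it for hybrid surgery. It is unsupported for this population, not shown to be false.
2. The stated 90% is not what the planned analysis delivers with 20% dropout. This shortfall comes from the dropout arithmetic and is separate from the sourcing. At the planned 5 points the power is about 81% for the ANOVA and 78% for one collar arm against no collar. Among the contrasts examined that fit the stated means, only the unplanned pooled one passes 90%.
3. The power statement does not extend to the choice between 3, 6 and 12 weeks.

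The figures assume SD 5, two-sided 5%, equal means in the collar arms and exactly 16 completers per arm. The 78% is for an unadjusted two-group t-test; Dunnett's adjustment for three comparisons with no collar would lower it. This should be corrected, but it does not invalidate the trial.

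**What to change.** Keep N at 80 and amend the article's text.

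- **Sample size calculation, source.** State that the 5-point gap is an assumed target difference carried over from fusion patients. Keep the citation of 23–25 for the SD if that is its source; deleting it outright would leave the SD without any.
- **Sample size calculation, power.** Replace 90% with the power of the planned analysis after dropout: about 81% for the four-group ANOVA and 78% for one collar arm against no collar, at two-sided 5%. Add 2, 3 and 4 points as an assumed sensitivity range (ANOVA 18%, 36%, 60%; pairwise 20%, 38%, 59%). Say that the figure covers only collar versus no collar.
- **Statistical analysis.** State that comparisons between 3, 6 and 12 weeks will be reported as estimates with 95% confidence intervals. State also that a non-significant result will not be read as showing that durations are equal or that a collar is unnecessary.

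The cost is wording only, with no extra patients. The downside is a less favourable stated power and a softer conclusion on duration, both in keeping with a trial described as exploratory.

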### Blinding

After randomization, patients will not be blinded to whether they will wear a cervical collar. Except for the follow-up personnel, other researchers—including the statisticians, outcome assessors, and data analysts—will all be blinded to the group assignments. The follow-up personnel will not be involved in the outcome assessment or data analysis. The design is open label with outcome assessors, data analysts being blinded, so unblinding will not occur.

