### Outcomes

#### Primary outcome

We chose the Neck Disability Index (NDI) functional score as the primary study endpoint. The NDI was proven to have better reliability, validity, and responsiveness for self-rated disability for postoperative patients [34]. The NDI will be evaluated postoperatively and at the 1^st^ week, 3^rd^ week, 6^th^ week, 3^rd^ month, 6^th^ month, and 12^th^ month after surgery. The NDI consists of ten items, including pain intensity, personal care, lifting, sleep, driving, recreation, headaches, concentration, reading, and work. Each item is scored out of 5 for a maximum total score of 50. Neck functions will be assessed by this score for all patients [35].

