#### Secondary outcomes

The secondary outcomes will include clinical, radiologic, and complication assessments. The assessment will be conducted prior to the operation and subsequently after the operation, continuing up to a period of 12 months post-operation or until the conclusion of the study (Table 1 and Fig. 2). The clinical and radiologic examinations will be performed by investigators who have no therapeutic relationship with the individual patient. All radiographs will be examined independently by one radiologist.

**Table 1 Tab1:** Data collection

Variables	Baseline	Follow-ups					
	Preoperation	1^st^ week	3^rd^ week	6^th^ week	3^rd^ month	6^th^ month	12^th^ month
Screening for inclusion and exclusion criteria	√						
Informed consent	√						
Randomization	√						
Baseline demographics	√						
Information collected through telephone follow-up/subjective scales							
NDI	√	√	√	√	√	√	√
JOA	√	√	√	√	√	√	√
VAS	√	√	√	√	√	√	√
PSQI	√	√	√	√	√	√	√
BDS	√	√	√	√	√	√	√
FES	√	√	√	√	√	√	√
Information collected through questionnaire follow-up/subjective scales							
SF-36	√	√	√	√	√	√	√
Cervical collar satisfaction score		√	√	√	√	√	√
Information collected through physical examination/objective scales							
Neck soft tissue assessment	√	√	√	√	√	√	√
Braden Scale		√	√	√	√	√	√
Information collected through radiologic examinations							
Cervical lordosis	√	√		√	√	√	√
ROM of C2-C7	√	√		√	√	√	√
Disc angle of the operative levels	√	√		√	√	√	√
ROM of the operative levels	√	√		√	√	√	√
ROM of the adjacent levels	√	√		√	√	√	√
Disc height of the operative levels	√	√		√	√	√	√
Fusion rate		√		√	√	√	√
Complications							
Anterior bone loss		√	√	√	√	√	√
Prosthesis migration		√	√	√	√	√	√
Heterotopic ossification		√	√	√	√	√	√

*JOA* Japanese Orthopedic Association, *NDI* Neck Disability Index, *VAS* visual analog scale, *PSQI* Pittsburgh Sleep Quality Index, *BDS* Bazaz dysphagia scoring system, *FES* Falls Efficacy Scale, *SF-36* MOS 36-item short-form health survey, *ROM* range of motion

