#### Objective scales

8.Neck soft tissue assessment and the Braden Scale will be used to evaluate Neck soft tissue injury extent within 10 cm around the collar position of patients in the collar groups [41] (Table 1 and Fig. 2).

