### Data collection

To ensure a satisfactory follow-up rate, we chose telephone follow-up to evaluate the NDI, JOA, VAS, Pittsburgh sleep quality index, the Bazaz dysphagia scoring system, Falls Efficacy Scale, and cervical collar satisfaction score. Since responding to many items is time-consuming for patients, the SF-36 health survey will be collected through questionnaires. When collecting data, the repeated parts will be asked only once to lower the confusion and improve the follow-up rate. Complications and cervical imaging parameters need to be evaluated through radiographs and CT. For a higher follow-up rate, healthcare professionals are to be reminded regularly (Table 1 and Fig. 2).

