Previous studies have merely selected NDI, SF-36, bone fusion rate, and imaging methods to observe the results of cervical collar wearing [20, 23–25]. In addition to selecting NDI as the primary outcome, we also designed detailed secondary indicators to monitor the possible complications caused by collar use. For instance, the JOA and the Bazaz dysphagia scoring system scoring system will be used to assess the impact of cervical collars on patients' daily life, while patients’ sleep quality will be monitored using the PSQI. Moreover, the cervical collar satisfaction score is designed to evaluate the feelings of patients with cervical collars from a subjective perspective.

Compared with previous studies [20, 23–25], we have added more details since our follow-up time may be extended to up to one year. Moreover, we used a variety of methods to evaluate the effectiveness of neck braces. Since patients often cannot return for reassessments, we opted to use phone calls for follow-ups. Radiographs and CT scans are necessary to evaluate complications and cervical imaging parameters; thus, we would allow such patients to have it done at their local hospitals. To guarantee a rigorous scientific study, patients will be screened strictly in accordance with the inclusion and exclusion criteria. Next, physicians will teach each patient how to correctly wear their neck braces to avoid unnecessary impacts on the ultimate findings. Finally, for patients who are not wearing neck braces, it is imperative that we explain the reasons in detail to reduce the placebo effect.

Nevertheless, there are several limitations to our study design. First, our trial is a single-center study; therefore, generalizing our findings to other centers should be done cautiously. Second, patients cannot be blinded in our study since the intervention is evident.

In summary, our study aims to utilize a rigorous design to comprehensively explore the effectiveness of cervical collar use by assessing various outcome measures following hybrid surgery. As a result of this trial, the feasibility of the protocol will be assessed, and a postoperative recovery strategy that is more considerate of patients and minimizes complications will be developed.

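### The statement that all outcome assessors are blinded is not supported by the article's own account of how the neck tissue scales and the NDI are collected

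*Protocol article*

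**What the plan says.** All references are to the protocol article.

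- **Blinding.** Patients know whether they wear a collar. For staff the section says: "Except for the follow-up personnel, other researchers—including the statisticians, outcome assessors, and data analysts—will all be blinded to the group assignments". It adds that "The follow-up personnel will not be involved in the outcome assessment or data analysis", and it closes by calling the design open label with blinded assessors and analysts, so that no unblinding can arise.
- **Primary outcome.** The NDI is the primary endpoint. It is chosen for its "responsiveness for self-rated disability for postoperative patients", so the patient is the rater.
- **Data collection.** "we chose telephone follow-up to evaluate the NDI, JOA, VAS, Pittsburgh sleep quality index", followed in the same sentence by the Bazaz and Falls Efficacy scales and the collar satisfaction score. The SF-36 alone goes by questionnaire.
- **Table 1 (Secondary outcomes).** The NDI, JOA, VAS, PSQI, Bazaz and Falls Efficacy rows stand under "Information collected through telephone follow-up/subjective scales". The collar satisfaction score stands under the questionnaire heading instead, at all six postoperative visits.
- **Objective scales.** Neck soft tissue and the Braden Scale are used to judge injury "within 10 cm around the collar position of patients in the collar groups".
- **Discussion.** "Since patients often cannot return for reassessments, we opted to use phone calls for follow-ups". The limitations paragraph admits that patients cannot be blinded and says nothing about assessors.

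**The concern.** In an open-label trial with a self-rated primary outcome, blinding whoever collects the ratings is the one protection left at the point of measurement. The Blinding section claims it for every assessor without exception. Elsewhere the article describes one assessment that cannot be done blind to collar status, and one telephone procedure that can disclose the arm.

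Two things are at stake. A caller who knows the arm may prompt or score ten verbally administered items differently by arm, in either direction. And a results paper that repeats the Blinding section would claim blinded assessment of the primary outcome, which the plan does not secure.

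**Working it through.** The plan gives no figure on this point, so the check sets the statements side by side.

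**1. Neck soft tissue and Braden Scale.** The Objective scales section ties both to the collar position in collar-group patients. An examiner who follows it knows that the patient was assigned a collar, though not necessarily for how long. This contradicts the claim that all assessors are blinded. Both scales are secondary outcomes, so this step says nothing about the NDI. The safeguard under Secondary outcomes, that examiners are not treating the patient, gives independence and not blinding.

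**2. Who rates the NDI.** The patient does, and the patient is unblinded. The article discloses this. A statement that outcome assessors are blinded therefore cannot describe the rating itself. It can at most describe the person who takes it down.

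**3. Who takes it down.** The calls are described by mode (telephone follow-up) and no staff group is named. The only staff whose title contains the word are the follow-up personnel, who are unblinded and are said not to assess outcomes. The article neither confirms nor excludes that they make the calls.

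**4. What a blinded caller would learn.** Under Data collection, the satisfaction score is obtained in the same telephone follow-up as the NDI. A question on contentment with collar use can disclose collar versus no collar. The order of questions is not stated, so the NDI of that same call may be exposed. Even if the NDI comes first, the answer at week 1 can inform the remaining 6 − 1 = 5 NDI calls if the same person calls again. Table 1 removes this route by listing the score under questionnaires, so the article disagrees with itself.

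**5. Extent.** Postoperative NDI assessments: 80 patients × 6 visits = 480; with the planned 20% dropout, 64 × 6 = 384. Carry-over calls after the first: 80 × 5 = 400, or 64 × 5 = 320. These are upper bounds, because they suppose that every caller knows or learns the arm.

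**6. Hypothetical size.** Caller bias is assumed at 0.5, 1 or 2 NDI points out of 50; nothing in the documents supports a particular value. The SD is 5 (Sample size calculation), with 20 × 0.8 = 16 evaluable per arm.

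- SE of a two-arm difference = 5 × √(2/16) = 1.768. The critical difference is t(0.975, 30 df) × 1.768 = 3.61 points.
- With no true difference, the two-sided false-positive rate from the noncentral t distribution with noncentrality bias/1.768 is 5.9%, 8.5% or 19.5%, against a nominal 5%.
- If the bias works against the planned 5-point difference, a bias of 1 or 2 points leaves 4 or 3 points, and the power of one pairwise comparison falls from 78% to 59% or 38%.

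Any bias of that size would give the same figures, including one from the patients' own expectations. They illustrate sensitivity and do not estimate an effect.

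**The case against.** A reader might go further and conclude that the unblinded follow-up personnel collect the primary outcome, so that the article flatly contradicts itself on the NDI. The documents do not support that. It rests on the shared word follow-up. The sections also fit together if blinded assessors make the calls and follow-up personnel handle contact, scheduling and collar use. Who makes the calls is also a detail that a condensed article may leave to the full protocol.

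Four further points count on the other side:

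- Patients' knowledge of their arm is disclosed under Blinding and again as a limitation, so it is not a hidden defect. For a self-rated scale it probably matters more than the caller's knowledge.
- Nothing restricts the satisfaction score to collar wearers. Table 1 sets no such limit, and the scale's description speaks of participants generally. Being asked the question need not reveal the arm; the answer can.
- The neck tissue assessment does not bear on the NDI.
- Staff who assign or teach collar use ("physicians will teach each patient how to correctly wear their neck braces") necessarily know the arm. Nothing shows that they assess outcomes, so their role does not undermine the claim about assessors.

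All of this stands, and it confines the point to its narrower form. The conflict over the neck tissue scales remains, because it lies in what the article states. So does the telephone route, because the Data collection section creates it whoever makes the call. Disclosure of patient unblinding does not repair a separate sentence that says assessors are blinded without exception.

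**Conclusion.** The point holds as an unsupported blinding claim. It does not show that the NDI is collected by unblinded staff.

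- **Contradicted by the text:** blinding of the neck soft tissue and Braden assessor (two secondary scales).
- **Not secured by the text:** blinding of whoever collects the NDI, because the caller is unnamed and the satisfaction score in the same telephone follow-up can disclose the arm.
- **Not in dispute:** blinded radiograph reading and blinded data analysis.

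The reach is at most 480 postoperative NDI assessments, or 384 after dropout. The size of any resulting bias is unknown. The article should be corrected, because the change is nearly free and otherwise the report would claim a protection that the plan does not provide.

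**What to change.** 1. **Data collection.** Collect the collar satisfaction score by questionnaire, as Table 1 already has it, and keep the answers from the callers. Ask the NDI first in every call.
2. **Callers.** Have existing staff without access to the allocation make the calls, and say so. Where this is not possible, and for calls already made by someone who knew the arm, report the NDI as collected unblinded.
3. **Blinding.** Limit the claim to radiograph reading, statisticians and data analysts, and add the callers only if they are in fact blinded. Describe the NDI as a patient-reported outcome from unblinded patients, and the neck tissue assessment as unblinded. Remove the assurance that no unblinding can arise.

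The cost is a small change in call procedure, two edits to the text and a less favourable blinding statement. No extra staff, visits or instruments are needed. Patients may still mention the collar during a call, and bias from their own knowledge of the arm remains. The change closes one route and corrects the claim; it does not make the primary outcome blinded.
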